### Evaluation of Feasibility

Feasibility will be evaluated by collecting data on the following: recruitment and retention rates; time required to recruit to target; attrition rates; feasibility of pre- and postintervention assessment and data collection methods, including completion rates; adverse events.

### Data Management

The study is compliant with the Data Protection Act 2018. All personal information (contact details, date of diagnosis, medical and social history) will remain confidential. Each participant will be given a unique research number, which will be used on all paperwork, in the names of video files and electronic records (eg, assessment data), and in analysis documents and subsequent publications. All data will be stored securely on Data Safe Haven, in accordance with the Data Protection Act 2018 and the sponsor’s data protection policy.

Video recording of conversation samples between dyads is required as an outcome measure and for video feedback during the intervention. Participants will consent to being video recorded for these purposes. Faces are required to be visible for detailed analysis of the video recordings, as natural human communication is the focus of the intervention being piloted. Only the research team will have access to the full video-recorded data set. Participants will be given the choice to opt in or out of the additional use of short extracts of video recordings for presentations about the research to professional audiences, teaching purposes, and as part of an online therapy resource. It is made clear in the PIS that there are risks of being recognized, and participants will be given a choice as to whether videos are masked (voice and image altered to reduce recognizability) if used for these purposes. They can opt out of videos being used in this way at any point during the study.

No data management committee will be established as it is felt that this short, small-scale pilot carries minimal risks. If any information is disclosed by the participant that leads the chief investigator to believe that a participant is at risk of harm or harming others, then confidentiality will be broken to ensure the safety of the person or people involved.

### Data Analysis

Quantitative and qualitative methods will be used to analyze the study data. Descriptive statistics will be used to report on recruitment, attendance, and attrition. Recruitment and retention rates will be used to support sample size calculations to inform a future full trial and plan the required number of sites to meet this target. To inform a sample size calculation, the mean pre- and postintervention scores, a mean change score, 95% CIs, and SDs will be calculated for each outcome measure. The mean change scores and standard deviations will be entered into the G*Power software, and an effect size will be calculated; this will then inform a 2-tailed sample size calculation for each measure.

Recordings of adverse events and participant feedback will be used to inform future recruitment procedures. The analysis of acceptability data will be based on participant feedback forms, interviews, and adherence data. This data will be analyzed using descriptive statistics and reflexive thematic analysis [40].

Speech, communication, and quality of life assessment data will be entered into a database and analyzed using SPSS (IBM Corp). This information will be used to determine a suitably sensitive outcome measure for a next-stage clinical trial, should this be warranted. Conversation outcomes will be captured using a procedure developed for Better Conversations with Aphasia to identify changes in the use of targeted strategies following intervention [23]. This will involve analysis of frequency counts of barrier and facilitator behaviors linked to people’s personal goals for intervention in 5-minute video samples selected from the midpoint of each of 6 pre- and postintervention conversation samples. We hypothesize that dyad management of problems with intelligibility (repair) may be a key site of conversation change. Intelligibility problems typically involve both speakers in a dyad over a series of conversational turns [41]. Given this, a secondary evaluation of conversation data will be conducted using Conversation Analysis [42].

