### Sample Size Justification

The recruitment of participants will be dealt with pragmatically, within the scope of a small feasibility pilot study. Based on related research and discussions with clinicians at the collaborating NHS Trust, who estimate an active caseload of people living with Parkinson’s of approximately 90 cases (inclusive of swallowing and communication difficulties), it is judged that it will be possible to identify and recruit 10-12 couples over a 6-month period. This allows for a slight overrecruitment to ensure 10 complete data sets.

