### Limitations

As a small-scale feasibility study with 10-12 dyads from 1 NHS site, the study is limited in scope. The study will therefore not seek to evaluate effectiveness or to generalize results beyond the participants. As a case-series study, which aims to describe the characteristics and outcomes at an individual level of a group of participants with Parkinson’s, this study does not include a control group. The results of the study will guide future phases of research into the BCP intervention, which if appropriate may involve a randomized controlled trial design.

A possible risk is a lack of diversity due to recruiting from 1 geographic area and an SLT caseload. Ascertainment bias is also possible: outcomes may be affected by factors (eg, socioeconomic status and cultural and linguistic barriers) that might be limiting access to the local speech and language therapy service. Despite the provision of a device to access the research, exclusion is possible as a result of digital poverty due to the requirement to have an internet connection to take part. Due to resource limitations, the research assistant will carry out the initial assessment and intervention. There is a risk that participants will not feel able to be completely open with feedback following each therapy session as the SLT delivering therapy is a member of the research team. The postintervention assessment and follow-up interviews will be completed by trained junior researchers to ensure that they are unaware of premeasure values and to provide an opportunity for participants to provide feedback they might not want to disclose to the SLT research assistant.

Personalization is a key element of this therapy approach. The coproduction group, which involves people with Parkinson’s and SLTs, has created a core set of activities and session plans to be used across all participants but has confirmed that personalization is essential. It is recognized that tailoring the intervention to different dyads and their goals may result in variation in the types of strategies identified and practiced; however, the session objectives, activities, and feedback tasks will be the same for all.

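### The main-trial sample size is to come from an uncontrolled pre-post change in about 10 dyads, which does not estimate a between-group difference and is too imprecise to size a controlled trial

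*Protocol article*

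**What the plan says.** The protocol article makes a sample size calculation the fourth of its five aims (Aim) and an estimated sample size the fourth of its four conditions for moving to a next-stage trial (Criteria for Success).

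Data Analysis describes the method. First, "the mean pre- and postintervention scores, a mean change score, 95% CIs, and SDs will be calculated for each outcome measure". Then, "The mean change scores and standard deviations will be entered into the G*Power software, and an effect size will be calculated". On the use to be made of that effect size, the article adds: "this will then inform a 2-tailed sample size calculation for each measure". The stated purpose is to plan a future full trial and its number of sites.

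The pilot supplying these inputs is small and has one arm. Sample Size Justification says "The recruitment of participants will be dealt with pragmatically, within the scope of a small feasibility pilot study", and of the 10-12 couples sought, "This allows for a slight overrecruitment to ensure 10 complete data sets". Limitations says "this study does not include a control group". It describes later research as work "which if appropriate may involve a randomized controlled trial design", and says of this study, "The study will therefore not seek to evaluate effectiveness".

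**The concern.** With one arm, the only effect size available is the mean pre-post change over some standard deviation. A controlled trial is powered on the difference between arms, and these data cannot separate that difference from change that controls would also show. Sources of such change include regression to the mean, repeated testing, attention and a change of assessor. On the last, Outcome Measures has the research assistant, who also delivers the therapy, take the pre-intervention measures, while junior researchers take the repeat measures.

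The estimate would also be very imprecise at 10 dyads. Confidence intervals are planned, but the text carries only the mean changes and SDs into G*Power. An aim and a progression criterion could therefore be met by a number that says little about the size of trial needed.

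**Working it through.** **Inputs from the article.** One arm; 10 complete data sets; effect size from mean change and SDs; two-tailed calculation. No main-trial N, effect size, SD, alpha, power, allocation ratio or test family is given, so there is no main-trial figure to reproduce. The pilot N was set pragmatically.

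**Assumptions for illustration.** Two-sided alpha 5%, planned power 80%, 1:1 allocation, t tests, standardized effects of 0.3, 0.5 and 0.8. None of these comes from the article, apart from the test being two-tailed.

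**1. Precision of the effect at n=10.** Set t = d√10, find the noncentrality values that put 2.5% in each tail of a t distribution with 9 df, and divide by √10.
- d = 0.8: t = 2.530; noncentrality 0.206 to 4.752; 95% CI 0.07 to 1.50.
- d = 0.5: t = 1.581; noncentrality -0.545 to 3.631; 95% CI -0.17 to 1.15.

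In the approximate two-sample formula, n per arm = 2(1.960 + 0.842)²/d² = 15.7/d². The limits for 0.8 then give about 15.7/1.50² = 7 and 15.7/0.07² = 3,200 per arm.

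**2. Precision of the SD at n=10.** The 95% limits are the observed SD times √(9/19.02) = 0.69 and √(9/2.70) = 1.83.

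**3. Change shared with controls.** Size a two-arm trial with the full pre-post effect d, then let controls show a fraction f of it. The true effect is d(1-f) and the noncentrality is d(1-f)√(n/2).

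| Planned d | n per arm | f = 0 | f = 25% | f = 50% | f = 75% |
|---|---|---|---|---|---|
| 0.5 | 64 | 80% | 56% | 29% | 11% |
| 0.8 | 26 | 81% | 56% | 29% | 11% |

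At f = 50%, restoring 80% power takes 253 per arm (true effect 0.25) or 100 per arm (true effect 0.4).

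**4. If a paired routine were used.** This is one possible reading. The smallest n giving 80% power:

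| d | Paired, total | Two-arm, total | Ratio | Power if the paired total is split in two |
|---|---|---|---|---|
| 0.3 | 90 | 352 | 0.26 | 29% |
| 0.5 | 34 | 128 | 0.27 | 29% |
| 0.8 | 15 | 52 | 0.29 | 30% (7 and 8) |

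**5. Sampling error carried into N.** In 20,000 simulated pilots of n=10, each trial was sized by the two-sample formula from the pilot estimate, keeping only pilots with an estimate above 0.1. For true effects of 0.8 down to 0.3:
- No change in controls: true power is below 80% in 53-69% of runs and below 50% in 23-49%.
- Half the change also in controls: below 80% in 88-93% and below 50% in 76-83%.

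**6. The opposite direction.** Suppose controls do not change, the pilot effect is 0.5 in SD-of-change units, and the pre-post correlation is ρ. In raw-score units the effect is 0.5√(2(1-ρ)), and a baseline-adjusted analysis needs 15.7(1-ρ²)/effect² per arm. For ρ = 0.3 this is 15.7 × 0.91/0.592², which gives 41. For ρ = 0.5 it is 15.7 × 0.75/0.5², which gives 48. Both are below the 64 planned, so the calculation can also overshoot.

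**The case against.** The strongest reply is that the article fixes less than a critic might assume.

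A reader might infer that G*Power's matched-pairs routine will be used, so that the answer would be for another one-group study. The article names only the software and a two-tailed calculation. It does not say which SD is used, and the software also sizes two-group comparisons. Those details may stand in a fuller document. This stands, so the 15 versus 52 contrast is conditional.

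A reader might also infer that a randomized trial is the settled next step. The article says only that one may follow, and the Discussion also mentions comparing face-to-face with telehealth delivery. This stands too.

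A third inference is that the future trial is bound to be badly underpowered. The article gives no effect, SD or control-arm change. The error runs from none to severe, and overshooting is possible (step 6).

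Finally, declining to evaluate effectiveness limits the claims made; it does not forbid a planning estimate. The effect size is said only to inform the calculation, and SDs and CIs are already planned. There is tension with Limitations, but no outright contradiction.

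None of this rescues the input. Whichever routine is chosen, an uncontrolled change cannot supply a between-group effect, and step 3 already uses the two-sample formula.

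**Conclusion.** The point holds as a fault in a stated method. The planned effect size is a within-group change from about 10 dyads. It does not estimate the between-group difference a controlled trial would target, and its 95% CI is too wide to fix a sample size. The resulting N could be far off, more likely too small, because shared change pulls that way and sampling error at n=10 leaves true power short of 80% in more than half of the simulated runs even without shared change.

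The size of the error cannot be fixed from the article. Under the assumptions above, true power ranges from about 80% to 11% with a two-sample formula. It would be about 30% if a paired total, roughly one quarter to one third of the two-arm total, were split between two arms. The conclusion applies to any controlled next-stage trial and does not require that a randomized one be certain. Nothing in the conduct of the pilot itself is affected.

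**What to change.** In Data Analysis, replace the step that turns the observed mean change into the effect for the sample size:
- Report the pre-post change and its standardized size for each measure as descriptive only.
- Use the pilot for the SDs with their CIs, the pre-post correlation and retention.
- Calculate the sample size for a controlled design, for example a baseline-adjusted two-arm comparison. Take the target difference from outside these data, such as a justified minimal important difference or a worthwhile change agreed with the steering group.
- Use a conservative SD, such as its 80% upper one-sided limit. At n=10 this is √(9/5.38) = 1.29 times the observed SD, so N is multiplied by 1.67.
- State alpha, power and test, and report a range of N.

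For scale, target differences of 0.3, 0.5 and 0.8 of the observed SD with that inflation give 292, 106 and 42 per arm before baseline adjustment, from 15.7 × 1.67/d². Without the inflation the same formula gives 175, 63 and 25.

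Reword the fourth aim and the fourth success criterion to match. The cost is a few sentences and no new data. The drawback is that the estimate becomes a range and may be larger than under the current method, depending on the target difference and the correlation.

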**Methods:**

Ethical approval for this study was obtained from London-Central Research Ethics Committee (reference: 22/LO/0332). This case-series feasibility pilot study will recruit 10-12 dyads to ensure 10 complete data sets. Participants will be recruited by a collaborating NHS site located in England. Participants will be involved for 16 weeks (weeks 1-2 preintervention measures, weeks 3-8 intervention, weeks 10-12 postintervention measures, week 16 follow-up interview). Quantitative and qualitative methods will be used to analyze the study data. Speech, communication, and quality of life assessment data will be analyzed statistically to determine a suitably sensitive outcome measure. Descriptive statistics will be used to report on recruitment, attendance, and attrition. Finally, acceptability and feasibility will be evaluated using participant feedback, interviews, and the reflective diary and feedback of the SLT administering the therapy (by the research assistant who is the first author). This data will be analyzed using descriptive statistics and reflexive thematic analysis.

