### Outcome Measures

Participants will complete preintervention speech, intelligibility, functional communication, and quality of life measures (Multimedia Appendix 1) with the research assistant in weeks 1-2 of the study. Questionnaires will be delivered via a mutually accessible platform (eg, Microsoft Teams or Zoom) or through an electronic questionnaire depending on participant choice, as recommended by the research steering group. Participants will be interviewed to establish a profile of their typical interactions [36], the types of problems with interaction they experience, how often these occur, and in what situations they arise. This will include the perspectives of the person living with Parkinson’s and their CP. They will also complete a case history, a rating scale of Parkinson’s symptoms, and a cognition and speech assessment to allow a description of relevant individual participant characteristics. This preintervention assessment protocol mirrors routine speech and language therapy practice. Furthermore, it provides the opportunity for the research assistant to build rapport with participants before delivering the intervention.

After intervention, measures (Multimedia Appendix 1) will be repeated (weeks 9-12). These assessments will contribute to the identification of a primary outcome measure for a future trial, if this is warranted. Final follow-up interviews and the Better Conversations Self Rating Scale will take place 8 weeks after treatment to understand long-term acceptance and the impact of the intervention. This will include the perspectives of both the person living with Parkinson’s and their CP. Repeated measures and the follow-up interview will be conducted by junior researchers (student SLTs) with training and support from the chief investigator and research assistant.

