### Criteria for Success

The study will be considered appropriate for a next-stage clinical trial evaluating the intervention if (1) the intervention is acceptable to people with Parkinson’s and their CP, (2) the intervention is feasible to deliver for the SLT, (3) a suitable sensitive outcome measure is identified, and (4) an appropriate sample size is estimated.

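### The same 10 or so uncontrolled dyads are used to choose the future primary outcome for its sensitivity and to supply its effect size, with no safeguard against selection

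*Protocol article*

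**What the plan says.** The Methods paragraph of the Abstract makes the choice of measure a statistical one, based on this study's own data: "Speech, communication, and quality of life assessment data will be analyzed statistically to determine a suitably sensitive outcome measure". The Outcome Measures section ties the repeated assessments to the future primary outcome: "These assessments will contribute to the identification of a primary outcome measure for a future trial, if this is warranted". The Data Analysis section states the same purpose: "This information will be used to determine a suitably sensitive outcome measure for a next-stage clinical trial, should this be warranted".

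That section also describes the sample size step. Mean pre and post scores, mean change, 95% CIs and SDs are calculated for each measure. The mean change and SD go into G*Power to give an effect size, and "this will then inform a 2-tailed sample size calculation for each measure".

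The Sample Size Justification plans 10-12 couples and adds: "This allows for a slight overrecruitment to ensure 10 complete data sets". Limitations confirms that there is no control group. Criteria for Success makes both products conditions for moving on: criterion 3 is that "a suitable sensitive outcome measure is identified", and criterion 4 is that a suitable sample size has been estimated.

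**The concern.** One small data set does two jobs. It shows which measures look responsive, and it supplies the effect size that sizes a trial on the measure chosen. An estimate picked partly because it came out large is too large on average, even if every estimate was unbiased before the choice. With about 10 dyads the sampling error is wide, so there is much room for this.

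The text names no external or minimum important difference, no shrinkage and no use of a lower confidence limit. The 95% CIs are calculated, but only the mean change and SD are said to enter G*Power. Two of the five aims (sample size, primary outcome) and two of the four success criteria depend on this step. An inflated effect would give a next trial with less power than its nominal figure.

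**Working it through.** **The plan's own figure.** No power-based figure exists to reproduce. The only arithmetic is the over-recruitment: 12 recruited with a loss of 2 in 12 leaves 10 complete sets, which is consistent.

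**Inputs from the article.** n = 10 complete data sets (Sample Size Justification); effect size from observed mean change and SD, two-tailed (Data Analysis); no control group (Limitations).

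**Assumptions, not in the article.** Alpha 0.05; power 80%; number of candidate measures K (Multimedia Appendix 1 is not shown; Outcome Measures names at least four domains); correlation rho between change scores; true effect; selection rule.

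**Step 1: precision.** Let dz = mean change / SD of change. With n = 10 and observed dz = 0.5, t = 0.5 × √10 = 1.58 on 9 df. Inverting the noncentral t gives a 95% CI for dz of -0.17 to 1.15.

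**Step 2: no selection.** With one measure fixed in advance and true dz 0.5, the median observed dz is about 0.51. A paired calculation then gives 32 pairs against the correct 34, with true power 78%. Small n alone barely shifts the median.

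**Step 3: selection.** Simulation of 20,000 pilots per setting, with equicorrelated normal change scores and the same true dz for every measure. The median selected dz goes into a paired t calculation: the smallest n whose noncentral t power (n - 1 df, noncentrality dz√n) reaches 80%. True power is then read back at the true dz.

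| Selection rule | Median selected dz, true 0.3 | Median selected dz, true 0.5 | Pairs implied, true 0.5 (34 needed) | True power, true 0.5 |
|---|---|---|---|---|
| Any of 8 with dz ≥ 0.2, rho 0.5 | 0.43 | 0.56 | 28 | 72% |
| Any of 8 with dz ≥ 0.3, rho 0.5 | 0.49 | 0.59 | 25 | 67% |
| Any of 8 with dz ≥ 0.5, rho 0.5 | 0.66 | 0.71 | 18 | 52% |
| Largest of 4, rho 0.8 | 0.48 | 0.69 | 19 | 54% |
| Largest of 8, rho 0.5 | 0.69 | 0.94 | 11 | 32% |
| Largest of 12, rho 0.3 | 0.84 | about 1.1 | 9 | 26% |

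In the threshold rows the choice is random among the measures that pass.

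**Step 4: unequal true effects** (rho 0.5, largest observed dz chosen; excess = selected dz minus that measure's own true dz).
- Four measures at true dz 0.1, 0.2, 0.3 and 0.8: the best is chosen 87% of the time; median excess 0.12.
- Eight measures evenly spread from 0 to 0.7: the best is chosen about 43% of the time; median excess 0.33.
- One measure at 0.6 and seven at 0.3: the best is chosen 44% of the time; median excess 0.36.

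**The case against.** The strongest reply is that the article never says the measure with the largest change wins. The wording is of a suitably sensitive measure, the aim is the most appropriate one, and the assessments only contribute to the choice. A threshold reading is fair and gives much less inflation. The rule may also stand in a fuller document. This stands, and it is why the size can only be a range. It does not remove the problem: any rule that leans towards larger observed change inflates in expectation, and the article states affirmatively that observed change and SD feed the sample size.

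A second reply is that equal true effects are an unfavourable case. This also stands. A reader might infer that the ranking of measures at n = 10 is mostly noise. The equal-effect simulation cannot show that, because it builds in equal measures. Step 4 shows that the risk of a wrong choice runs from small to substantial, depending on how far the measures truly differ.

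Third, a reader might turn the selected dz into a two-arm trial: at true 0.5, the largest of 8 would imply 19 per arm where 64 are needed. The documents do not support this as a prediction. A within-person dz is not a between-group effect, and Limitations says only that a randomised design may follow.

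Fourth, the plan reports every measure, not only the chosen one, and already collects completion rates and acceptability data. True, and it makes the fix cheap, but the article does not make these the grounds for choosing.

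**Conclusion.** The concern holds in a limited form. As written, the same data judge sensitivity and supply the effect size, without a safeguard, so the effect carried forward is biased upward to the extent that observed change drives the choice. At n = 10 and true dz 0.5, the median selected value lies between about 0.56 and 1.1 across the equal-effect rules examined. Paired power falls from the nominal 80% to between about 72% and 26%. The excess is smaller where one measure is clearly more responsive. These figures rest on assumed K, correlation, true effects and selection rule, none of which the article gives.

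A reader might infer that this bias would persist after the one-arm effect-size problem was repaired. That is too strong: if the repair is to size the trial on an external difference, selection no longer affects the sample size, and only the choice of measure remains exposed. The two points are best handled together.

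This should be fixed but is not critical. No participant is affected, the study disclaims any evaluation of effectiveness, and the future trial will set its own design.

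**What to change.** Amend Data Analysis, and align criterion 3 in Criteria for Success, as follows.

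- State that observed change is not the deciding ground for the future primary outcome. Use completion rates, floor and ceiling rates at baseline, relevance as judged by people with Parkinson's, conversation partners and therapists, and baseline repeatability where repeated baselines exist (the three preintervention conversation samples).
- Report mean change with its 95% CI for every measure, labelled descriptive.
- Size the next trial on an externally justified important difference. Use this study only for a conservative SD (for example an upper confidence limit) and for retention, not for the selected measure's own observed effect.

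The cost is a short ranking table and a few sentences. Most of the data are already planned; an external difference must be found and justified for each serious candidate. The downside is that the study gives up naming a most responsive measure.
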